### Randomisation

Since the interventions will be delivered at the group level, this trial is designed as a cluster cRCT where TB centres will be randomly allocated to the different trial arms. The TB centres (clusters) would be randomised in a 2:2:1 ratio to mTB-Tobacco (intervention A), face-to-face (intervention B), or standard care (Control). An independent statistician, blinded to clusters, will identify and use computer-generated random number lists to generate the allocation sequence. The allocation will be based on using minimisation to ensure balance across the groups on the average number of patients with TB seen per month and geographical locations (Bangladesh and Pakistan).

### Blinding

In this study, we used a blinding methodology to guarantee that specific key individuals remained uninformed about the allocation of treatments. The allocation sequence will be determined by an independent statistician, who has no knowledge of the participating facilities. Nevertheless, as the SMS receipt is a noticeable component, participants will be able to determine whether they are receiving the SMS or not. Therefore, it is not possible to achieve total blindness at the participant level in this circumstance. In addition, the principal investigator (PI) and the research teams are aware of the specific cluster assigned to each treatment group. However, steps will be taken to potentially prevent the data analyst from knowing the treatment assignments in order to reduce bias during the analysis of the data. Thus, the blinding in this trial will occur during randomising the clusters to intervention or control by an independent statistician and also at the level of data analyst while analysing the data.

### Treatment and control arms

#### mHealth-based mTB-Tobacco intervention

The mTB-Tobacco is an mHealth intervention, based on a smoking cessation package developed by the WHO that can be delivered as mobile SMS text messages to patients with TB.^16^ This package comprises two distinct areas of intervention, the first tries to instil behaviour change in patients to quit the habit of tobacco use and the second includes a combination of TB-related supportive motivational and informative messages. The package aims not only to inform patients with TB about the hazards of tobacco use and encourage them to quit, but also to enhance treatment adherence, increase healthy behaviours and reduce potentially harmful behaviours in patients with TB to improve their overall health outcomes.

The set of SMS text messages included in the mTB-Tobacco package was adapted by research experts to include 134 one-way messages, and a transmission schedule was designed to set the days for each message delivery along with a specified time. Each participant in the intervention group will receive a total of 134 SMS messages over 6 months. In the first 2 months, the frequency of messages would be 4–5 messages per day, in the next 2 months, the frequency would reduce to 1–2 messages per day, and in the last 2 months, there will be 1 message sent after a couple of weeks. The final list of messages and delivery schedule is given as online supplemental table 1.

The messages will be translated into local languages including Urdu and Bangla by local research teams, using the translation and validation steps recommended by the WHO.^17^ The initial forward translation will be carried out by an independent bilingual translator in local language, and the translated content was back-translated into the English language by another independent translator. The conceptual and cultural context will be taken into account. The discrepancies will be discussed with the local PIs and research team to make translations satisfactory.

A web-based digital application (mTB-Tobacco) will be developed by the local research team to sync the data with the database and send the SMS text messages automatically to the enrolled participant’s personal mobile numbers, following the set schedule. The mTB-Tobacco web portal will store the participant’s unique ID number and active mobile number for the trial. No other personal or identifiable information will be stored.

#### Face-to-face behavioural support (Intervention B)

This consists of an adapted version of a predeveloped and proven effective intervention to help people quit smoking and smokeless tobacco use.^9^ This consists of two face-to-face sessions delivered on day 0 and day 5 (+2) which last 10 and 5 min respectively. The sessions will be structured using an educational flipbook; the session on day 0 will be aimed at encouraging tobacco users to see themselves as non-users and set a plan for a quit date 5 days later; with a session on the quit date (day 5) to review progress. Further encouragement and support (if needed) will be offered at a subsequent visit in week 5.

#### Standardised usual care (Control)

In the usual care group, the patients will undergo routine TB treatment care. In addition, education leaflets will be given to the control arm participants. The leaflets, containing information on the harmful effects of tobacco and advice on stopping smoking, will also be given to the participants belonging to the intervention arms A and B.

### Study outcomes

#### Primary outcomes

The primary outcome will be biochemically verified continuous abstinence at 6 months postrandomisation.^18^ Abstinence is defined as a self-report of not having used more than five cigarettes, bidis, water pipe sessions since the quit date, verified biochemically by a breath carbon monoxide (CO) reading of less than 10 ppm at month 6.^18^

In case of concomitant smokeless tobacco use, biochemical verification will be carried out using COT Rapid Test Cassette (Hangzhou All Test Biotech) to detect cotinine (a nicotine metabolite) level in urine samples. The test result will be interpreted as ‘negative’ if two lines appear (one coloured line in the control line region and another apparent coloured line in the test line region) or ‘positive’ if one coloured line appears in the control line region. The negative result will indicate that the cotinine concentration is below the detectable level (200 ng/mL) while the positive result will indicate that the cotinine concentration exceeds the detectable level (200 ng/mL). The research assistant (RA) will perform cotinine dipstick tests on urine samples collected from the patients, which will be discarded after cotinine levels have been recorded on the case report forms (CRFs).

When a patient self-reports abstinence with an elevated CO level of >10 ppm (and cotinine levels in concomitant users indicating active tobacco use), the biochemical verification will supersede the self-report and the patient will be defined as a tobacco user.

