**Methods and analysis:**

A two-arm, parallel, open-label, multicentre, cluster randomised, two-stage adaptive design trial is proposed to first evaluate the superiority of mTB-Tobacco, compared with usual care and then the non-inferiority of mTB-tobacco compared with face-to-face behaviour support. Study settings include TB treatment centres in Bangladesh and Pakistan. The study population includes adult patients, newly diagnosed (within 4 weeks) with pulmonary TB disease, daily smokers, willing to quit and have access to mobile phones. The primary outcome includes biochemically verified continuous smoking abstinence assessed at 6 months per Russell Standard. A generalised linear mixed-effects model will be used to assess the impact of mTB-Tobacco intervention on continuous outcomes, incorporating fixed effects for the intervention, random effects for clusters and relevant covariates. Cost-effectiveness analysis will be done to estimate the cost per quitter and cost per quality-adjusted life year gained, calculate the incremental cost-effectiveness ratios to establish the value for money for mTB-Tobacco.

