#### Eligibility criteria for inclusion of participants

Participants aged 15 years or older, diagnosed with drug-sensitive pulmonary TB (smear positive or negative) in the last 4 weeks, currently smoking tobacco daily or have only stopped or reduced smoking (less than daily) since diagnosed with TB, willing to quit tobacco use, have access to personal mobile phone and willing and able to provide written informed consent (online supplemental file 1) will be included in the study. A smoker in this trial will be defined as ‘a TB patient who smokes cigarette, and/or biddi, and/or water pipe sessions daily, which means at least 25 days in last month; this does not include heated tobacco products for example, e-cigarettes’. A smoker, as per the mentioned definition, also using smokeless tobacco will be eligible to participate in the trial. Informed consent will be taken from adult participants (18 years and above), while assent along with parent/guardian’s consent will be taken for adolescent participants (15–17 years of age). Exclusion criteria include patients anticipated to have adverse effects either due to the study treatment or research burden. These will include those who are/have less than 15 years of age, retreatment TB, multidrug-resistant TB, miliary or extrapulmonary TB, currently using any pharmacotherapy for tobacco dependence and unwilling or unable to provide written informed consent.

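### The primary endpoint is defined on smoked tobacco, but in dual users it is verified by urine cotinine, so someone who stopped smoking and still uses smokeless tobacco can be scored a failure

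*Protocol article*

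**What the plan says.** The Abstract (Methods and analysis) names the outcome as "biochemically verified continuous smoking abstinence assessed at 6 months per Russell Standard". Under Primary outcomes, the self-report part is "not having used more than five cigarettes, bidis, water pipe sessions since the quit date", supported by a breath CO reading below 10 ppm at month 6. Smokeless products are not in that list.

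The participant eligibility section says that a smoker "also using smokeless tobacco will be eligible to participate in the trial". For these patients, Primary outcomes says: "In case of concomitant smokeless tobacco use, biochemical verification will be carried out using COT Rapid Test Cassette". The test is read as positive above 200 ng/mL, and the same paragraph describes cotinine as a nicotine metabolite.

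The override sentence covers a patient who reports abstinence but has CO above 10 ppm. It adds, in parentheses and joined by *and*, a cotinine result in concomitant users that indicates active use. In that case "the biochemical verification will supersede the self-report and the patient will be defined as a tobacco user".

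The only quit date described is in the face-to-face arm (Intervention B), where the day 0 session is to "set a plan for a quit date 5 days later". The sections on mTB-Tobacco (arm A) and usual care mention none.

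**The concern.** The definition and its verification measure different things in one eligible subgroup. The definition asks about smoking. Cotinine responds to nicotine from any tobacco, and its result is allowed to outrank the self-report. Because the override sentence can be read in two ways, two people scoring the same month 6 record could disagree on the primary endpoint.

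This is the trial's only primary endpoint, and its phase 3 result decides whether phase 4 is run. If true smoking quitters are counted as failures, observed quit rates fall in every arm and the absolute difference shrinks with them.

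A lesser matter is that continuous abstinence is counted from a quit date for which the article gives no start common to all arms. Patients who had already stopped after their TB diagnosis are eligible, so the start is open for them too.

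**Working it through.** **1. How the printed rules score a dual user who reports no smoking**

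| Month 6 state | Smoking definition | Cotinine decides | Both tests must be positive to override |
|---|---|---|---|
| CO <10, cotinine negative | abstinent | abstinent | abstinent |
| CO <10, cotinine positive (still uses smokeless) | abstinent | tobacco user | abstinent |
| CO >10, cotinine positive | not abstinent | tobacco user | tobacco user |

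The second row is the defect. The two readings disagree there, and the reading that follows the plain instruction to verify dual users by cotinine contradicts the definition. Under the joint reading, a positive cotinine never changes the result of a low-CO patient, which leaves that instruction with almost no function. Separately, a CO of exactly 10 ppm falls in neither the below-10 nor the above-10 rule.

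**2. The plan's phase 3 figures (Sample size)**

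- 704 participants / 27 centres = 26.07 per centre.
- Design effect = 1 + (26.07 − 1) × 0.02 = 1.50, as stated.
- 704 × 1.50 = 1056, or 39.1 per centre. Rounded up to 40, this gives 40 × 27 = 1080, as stated.
- With 20% attrition, 40 × 0.8 = 32 are analysed per centre. The 2:1 ratio gives 18 v 9 centres.

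**3. Dilution in phase 3**

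Let *q* be the share of true smoking quitters who fail cotinine because of smokeless use, equal in both arms. Then observed rate = true rate × (1 − *q*). The documents give no value for *q*, so 10% to 30% is an assumed range.

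The main power figure comes from simulated beta-binomial centres (ICC 0.02, 32 analysed per centre) and a centre-level t-test with 25 df at two-sided 5%. As a cross-check, the normal approximation uses effective n = 1080 × 0.8 / (1 + 31 × 0.02) = 864 / 1.62 = 533, split 2:1.

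| *q* | mTB-Tobacco | Usual care | Difference | Power, centre-level | Power, normal approx. |
|---|---|---|---|---|---|
| 0 | 18.0% | 8.0% | 10.0 | 87% | 90% |
| 10% | 16.2% | 7.2% | 9.0 | 83% | 85% |
| 20% | 14.4% | 6.4% | 8.0 | 78% | 80% |
| 30% | 12.6% | 5.6% | 7.0 | 71% | 73% |

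Separate simulation runs agree to about one point (82%, 77% and 70% at the low end). The ratio of rates stays at 18/8 = 2.25 throughout. The step from the planned 90% to 87% at *q* = 0 comes from the centre-level analysis and has nothing to do with this point.

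**4. Phase 4, conditional**

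Take true smoking quit rates of 18% in both arms. Let *s* be the share of quitters who are dual users and *f* the share of those who continue smokeless use, so observed rate = 18% × (1 − *s* × *f*). If *f* is the same in A and B, the expected difference stays 0. If, purely as an illustration, *f* is 75% in A and 25% in B:

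- *s* = 10%: 16.65% v 17.55%, difference −0.9 points
- *s* = 20%: 15.3% v 17.1%, difference −1.8 points
- *s* = 40%: 12.6% v 16.2%, difference −3.6 points

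The margin is 8 points. With 18 centres per arm and 45 × 0.8 = 36 analysed per centre, simulated non-inferiority power goes from 80% to 72%, 62% and 40%.

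**The case against.** The strongest reply has four parts.

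**The rule is the same in every arm.** This stands. It separates dual users from smoking-only users, not one arm from another. A reader might infer that the endpoint cannot be scored alike across arms, or that phase 4 is biased against mTB-Tobacco because arm B's package was developed to "help people quit smoking and smokeless tobacco use". The documents do not support that. The mTB-Tobacco section also aims at quitting tobacco use, and all arms receive leaflets on the harms of tobacco.

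**The intended target may be all tobacco.** Patients must be willing to quit tobacco use, failures are labelled tobacco users, and the secondary point-abstinence outcome refers to tobacco. Adding smokeless use to the self-report would also remove the inconsistency. This is a fair alternative, but it would change an endpoint that the Abstract and the definition both state as smoking.

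**The size is assumed.** This stands. The value of *q* is dual use multiplied by continued use, so 30% needs, for example, 60% × 50%. At 5%, power is still about 85%. The planning rates of 18% and 8% rest on a cited study whose verification rule is not shown. If it also failed such users, part of the loss is already in those rates.

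**The quit date may be settled elsewhere.** The arm A messages are in a supplement and the full protocol is not shown. A reader might infer that late quitters count in arm A and control but not in arm B. The article does not show this. In phase 3 neither arm has a described quit date, so the window is undefined in both rather than unequal. Arm B's date is a plan and is not stated to be the scoring date. The Introduction speaks of abstinence for at least 6 months, which sits badly with counting a month 5 quitter. Nor does much hang on the phrase "biochemically verified continuous abstinence at 6 months postrandomisation" in a trial that randomises centres: Study assessments sets the visits at day 0, week 9 and month 6, so this is wording.

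**Conclusion.** The inconsistency is in the printed text and needs no assumption: a low-CO dual user who has stopped smoking meets the definition and can be recorded as a failure, and the override sentence leaves the result open. It should be settled before the phase 3 analysis.

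The consequence is mainly loss of absolute difference and power, not favour to one arm. At an assumed 10% to 30% of true quitters, the 10-point difference becomes 9 to 7 points and phase 3 power drops by roughly 4 to 16 percentage points from about 87%. The true loss depends on a dual-use rate that the article does not give. A spurious difference between A and B in phase 4 requires continued smokeless use to differ between them; the figures for that case illustrate what could happen and are not a finding.

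The missing common start date is a secondary point. It holds for the article as printed and may be resolved in documents not shown.

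**What to change.** 1. Keep smoking abstinence as the primary endpoint and verify it by breath CO in every participant, dual users included.
2. Use cotinine only for a secondary all-tobacco abstinence outcome in dual users.
3. Reword the override sentence to match, so that CO alone decides the primary endpoint, and assign a reading of exactly 10 ppm to one side.
4. State one scoring start, counted from day 0 and identical in all arms, and say how patients who stopped before day 0 are scored.

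The cost is an amendment to the outcome definition. No new measurement is needed, because Table 2 already schedules CO for everyone at month 6. The downside is that CO detects only recent smoking, a limit that already applies to smoking-only participants. If the sponsor does intend all-tobacco abstinence, the definition and the Abstract would have to say so and the self-report would have to cover smokeless products.

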#### Secondary outcomes

The secondary outcomes include: point abstinence, defined as a self-report of not using tobacco in the previous 7 days, assessed at week 9 and month 6; Adherence to TB treatment: All registered patients with TB’s medication logs (for anti-TB medication) are recorded on the ‘Treatment Support Card’; a copy of this card would be requested from the TB paramedic by the RA and attached with the patient CRF; TB Programme outcomes: the proportion of treatment success (including cured and completed treatment), treatment failure, defaulted and died will be recorded from the TB register (TB03) at month 6; and Economic evaluation. Table 1 gives definitions of TB treatment outcomes.

**Table 1 T1:** Definitions of TB treatment outcomes as per guidelines

Sr. no.	TB treatment outcomes	Definition
1	Cured	A patient who was initially smear-positive and who was smear-negative in the last month of treatment (at month 6) and on at least one previous occasion.
2	Completed treatment	A patient who completed treatment (at month 6) but did not meet the criteria for cure or failure.
3	Treatment failure	A patient who was initially smear-positive and who remained smear-positive at month 6 or later during treatment.
4	Defaulted	A patient whose treatment was interrupted for two consecutive months or more.
5	Died	A patient who died from any cause during treatment.
6	Relapse	A patient who was previously treated for TB, was declared cured or treatment completed at the end of his most recent course of treatment and is now diagnosed with a recurrent episode of TB (either a true relapse or a new episode of TB caused by reinfection).

TB, tuberculosis.

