### Study assessments

All study participants will have assessments on day 0, week 9 and month 6 time points corresponding with routine TB clinic visits. All the trial activities will be performed by field RAs (one RA per site) who will be hired and trained to take patient consent, collect baseline data, follow-up data and perform study assessments. The trial assessment schedule, given as table 2, outlines the visit dates necessary for data collection, but the patient may be seen more frequently for routine clinical care as needed. During the treatment period, if study participants are unable to attend on the day, every effort would be made to complete the visit within 2 days of the scheduled date. If a scheduled visit is missed without notice, then the RA should endeavour to contact the patient by phone or by home visit.

**Table 2 T2:** Participant enrolment and follow-up assessment schedule for Quit4TB trial

Assessment	Screening	Day 0 baseline	Week 9	Month 6
Assessment of eligibility criteria	⌧			
Written informed consent	⌧			
Face-to-face/phone-based interaction			⌧	
Self-reported tobacco use/abstinence status		⌧	⌧	⌧
CO measurement				⌧
Sociodemographic information		⌧		
Tobacco use and quit history		⌧		
Nicotine dependency		⌧	⌧	⌧
Economic outcomes		⌧		⌧
Process outcomes (fidelity)			⌧	⌧
Medication (TB) compliance			⌧	⌧
Adverse events review			⌧	⌧
TB outcomes				⌧

CO, carbon monoxide; TB, tuberculosis.

During the follow-up phase, scheduled assessments will be carried out no more than 5 days before the scheduled visit. Scheduled visits will be rescheduled to allow for public holidays or other unavoidable circumstances that affect the scheduled visit date, but the rescheduled visit should be no more than 5 days from the originally scheduled visit date. Participants will also be given a card with the contact details for the trial RA and the clinical TB care team at their site. If a patient is more than 5 days late for a scheduled study visit, an additional visit will be performed as soon as possible, including the appropriate assessments that were specified in the trial schedule for the visit that was missed.

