#### Cost-effectiveness analysis

Health economic evaluation will be conducted to establish the value for money afforded by the mTB-Tobacco intervention. The cost of providing the interventions will be recorded and calculated using local cost data. Costs include staff, premises and pharmaceutical products. Patients’ wider use of public and private healthcare will also be recorded, using a self-report service use questionnaire. Patient cost profiles will be calculated by applying country-specific unit cost tariffs to quantities. Total intervention cost, costs of wider healthcare use and also patients’ out-of-pocket expenditure will be derived, and a total cost will be applied to each patient in each trial arm.

In the superiority trial (phase 3), an incremental cost-effectiveness analysis (CEA) of the mTB-Tobacco intervention will be conducted, over and above usual care. European Quality of Life 5-dimensions 5-levels (EQ-5D-5L) questionnaire will be used to calculate quality-adjusted life years (QALYs) using the area under the curve.^21^ Incremental cost-effectiveness ratios (ICERs) will be presented in terms of (1) cost per QALY and (2) cost per additional quitter as based on the secondary outcome of the trial. A 12-month time horizon is selected for the CEA to use the longer-term window of healthcare use and changes in health-related quality of life. A full sensitivity analysis will be presented to assess the robustness of the results and the probability that mTB-Tobacco intervention is cost-effective at a range of threshold values.

In a non-inferiority trial (phase 4), resource quantities and attribute unit costs will be recorded for the mTB-Tobacco intervention and face-to-face behaviour support, inclusive of wider health system costs following the methodology of the phase 3 superiority trial. Costs for each arm will be calculated and compared with a predefined acceptable cost difference. A CEA will also be done for the non-inferiority trial (phase 4). Differences in costs and QALYs between treatment arms will be estimated to calculate the ICER for the cost per QALY and cost per additional quitter.

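### Month 6 point abstinence rests on self-report alone, although CO is measured at that visit and cost per quitter apparently depends on this outcome

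*Protocol article*

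**What the plan says.** All places are in the protocol article.

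- **Secondary outcomes** lists "point abstinence, defined as a self-report of not using tobacco in the previous 7 days, assessed at week 9 and month 6". There is no biochemical condition and no reference back to the verification rule.
- **Primary outcomes** requires the self-report to be "verified biochemically by a breath carbon monoxide (CO) reading of less than 10 ppm at month 6". Users of smokeless tobacco as well also have a urine cotinine test. If someone claims abstinence but CO is above 10 ppm, "the biochemical verification will supersede the self-report and the patient will be defined as a tobacco user".
- **Study assessments, Table 2**: the row "Self-reported tobacco use/abstinence status" is marked at day 0, week 9 and month 6. The row "CO measurement" is marked at month 6 only.
- **Blinding**: "participants will be able to determine whether they are receiving the SMS or not". The research teams also know each cluster's arm.
- **Cost-effectiveness analysis**: one of the two ratios is "cost per additional quitter as based on the secondary outcome of the trial".

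**The concern.** At month 6 the trial holds two pieces of evidence on recent smoking: the participant's answer and a breath reading. The primary outcome uses both. The secondary outcome, as defined, uses only the answer. A participant who reports seven tobacco-free days and has a CO reading of 25 ppm counts as point-abstinent, although the trial's own measurement says otherwise.

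Participants know what they receive, and the research assistant who collects follow-up data works at one site and so in one arm. Over-reporting that differs by arm is therefore possible, and self-report is the abstinence measure most exposed to it.

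Two results are at stake: the month 6 point-abstinence comparison and, apparently, the cost per additional quitter. The article does not name the secondary outcome it uses for that ratio. The others listed are adherence to TB treatment, TB programme outcomes and the economic evaluation itself, so point abstinence is the only candidate that measures quitting.

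**Working it through.** The plan states no figure to reproduce on this point. The check compares the definitions and then illustrates the possible size.

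**1. Definitions at month 6**

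| | Primary outcome | Point abstinence |
|---|---|---|
| Period | since the quit date | previous 7 days |
| Source | self-report plus CO (cotinine for concomitant smokeless users) | self-report |
| Self-report contradicted by CO above 10 ppm | tobacco user | no rule stated; abstinent as worded |

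At week 9 no CO is scheduled, so self-report is all there is and the point does not arise.

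**2. Possible size (illustration only)**

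Inputs from Sample size: 18% and 8% abstinence at 6 months; 27 centres at 2:1, about 40 participants each, so 18 x 40 = 720 intervention and 9 x 40 = 360 control.

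Assumptions not in the documents:
- The planned rates stand in for true 7-day abstinence.
- A share f1 (intervention) or f0 (control) of people who are not abstinent report that they are.
- CO at month 6 exposes all of them.
- Follow-up is complete.

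Self-reported rate = p + (1 - p) x f. For example, 0.18 + 0.82 x 0.05 = 0.221 and 0.08 + 0.92 x 0.05 = 0.126.

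| f1 | f0 | Intervention | Control | Apparent difference |
|---|---|---|---|---|
| 0 | 0 | 18.0% | 8.0% | 10.0 points |
| 5% | 5% | 22.1% | 12.6% | 9.5 points |
| 10% | 10% | 26.2% | 17.2% | 9.0 points |
| 10% | 5% | 26.2% | 12.6% | 13.6 points |
| 15% | 5% | 30.3% | 12.6% | 17.7 points |
| 5% | 10% | 22.1% | 17.2% | 4.9 points |

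With no true effect (8% in both arms) the apparent difference is 0.92 x (f1 - f0): 0 points for 5% v 5%, 4.6 for 10% v 5%, and 9.2 for 15% v 5%.

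Participants counted as abstinent against their own CO reading:
- At 5% in both arms: 720 x 0.82 x 0.05 = about 30, and 360 x 0.92 x 0.05 = about 17.
- At 10% in both arms: about 59 and 33.

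Equal misreporting slightly dilutes the difference. Unequal misreporting can move it several points either way.

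**The case against.** **The outcomes differ by design.** The override stands under Primary outcomes, and point abstinence is expressly a self-report. Continuous and 7-day abstinence can properly disagree: someone who relapsed early and stopped later fails the first and meets the second. This stands. A reader might infer that the protocol contradicts itself, but the text does not support that. The override is also worded generally enough that it may be meant for both outcomes. If so, the case is already handled, but Secondary outcomes does not say so.

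**Comparability over time.** One self-report definition at both visits gives a consistent series, which would be lost if the month 6 definition were replaced. This stands, and is a reason to add a verified version and keep the existing one.

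**The main risk is already covered.** The primary outcome is verified. This stands, and it limits the importance of the point.

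**The size is assumed.** This stands. It is tempting to set a figure such as 4.6 points against the 10-point planned effect or the 8-point non-inferiority margin, but both were set for the 6-month abstinence used in the sample size, and the misreport rates are invented. In phase 4 both arms receive active support, and the blinding text does not show which arm would over-report more.

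**An analysis plan could add a verified version.** It could. But the article itself fixes the definition as self-report and ties a cost-effectiveness ratio to the secondary outcome, so the point is not merely an omission.

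**Conclusion.** The point holds as a weak outcome definition that is easily strengthened. Month 6 point abstinence ignores a reading taken at the same visit, in a trial where participants and research teams know the allocation. The month 6 secondary comparison is exposed, and so apparently is cost per additional quitter. That second step rests on reading the unnamed secondary outcome as point abstinence.

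The direction and size of any bias are unknown. The 4.9 to 17.7 points in the illustration show only how sensitive the outcome is to assumed misreporting. A reader might infer that the trial's main conclusion is compromised. It is not: the primary outcome carries its own verification, and the sample size does not use point abstinence. Week 9 is not at issue.

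**What to change.** 1. At month 6, add a verified 7-day point abstinence: self-report, plus CO below 10 ppm, plus the cotinine rule from Primary outcomes for participants who also use smokeless tobacco. Make it the main month 6 version.
2. Name this version as the basis for cost per additional quitter.
3. Keep the self-report outcome at week 9 and month 6 as one comparable series, labelled unverified, and show the two month 6 rates side by side.
4. Say in one sentence whether the override in Primary outcomes applies beyond the primary outcome.

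**Cost.** No new visit or CO test is needed, since CO is already scheduled. Recruitment began in February 2024 under approved version 5.0, so the addition needs a dated record, preferably made before outcomes by arm are seen. Verified rates will be lower, by an amount that depends on misreporting: under the illustration, by 4.1 points (0.82 x 5%) to 12.3 points (0.82 x 15%) in the intervention arm. The verified version exists only at month 6, so it cannot be compared with week 9. A rule is also needed for participants who report abstinence but give no reading.
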